#### **5.5.5 Premature end of trial/ Withdrawal of the whole study**

Reasons for premature termination of the entire study are:

- Decision including benefit-risk assessments of the study management when unacceptable risks and toxicities occur
- Consideration of termination for each grade 5 toxicity, 2 consecutive grade 4 toxicities, 5 consecutive grade 3 toxicities
- new (scientific) evidence during the study
- Inadequate recruitment rate

## **5.6 Prior and Concomitant Illnesses**

Relevant additional illnesses present at the time of informed consent are regarded as concomitant illnesses and will be documented in the patient chart. Abnormalities which appear for the first time or worsen (intensity, frequency) during the trial are adverse events (AEs) and must be documented on the appropriate pages of the CRF.

## **5.7 Prior and Concomitant Treatments**

Relevant additional treatments administered to the patients on entry to the trial or at any time during the trial are regarded as concomitant treatments and must be documented on the appropriate pages of the CRF. Patients having received neoadjuvant chemotherapy or neoadjuvant endocrine therapy cannot be included in the trial. During radiation therapy, medication required for concomitant illnesses (i.e. hypertension, thyroid disease, hyperlipidemia etc.) can be applied. Concomitant medication should be discussed with the principal investigator on an individual basis. No concomitant chemotherapy or any other anti-tumor medication except for hormone therapy is allowed during the treatment period in this trial.

# **6. Radiation Therapy**

## **6.1 Treatment Planning for APBI and dose prescription**

Patients will receive electron IORT with a total dose of 21 Gy prescribed to the 90%-isodose. Selection of the appropriate size and shape of the tube is at the discretion of the treating physician, but a minimum diameter of 1-2 cm in addition of the clinical tumor size is suggested. The tumor bed should be prepared according to the instructions by Veronesi et al. A lead or aluminum shield shall be inserted on the surface of the major pectoralis muscle to protect the thoracic wall. The linear accelerator delivers electrons at variable energies (6, 9 and 12 MeV). Depending on the target thickness the adequate electron energy is chosen.

## **6.2 Treatment Planning for whole breast irradiation and dose prescription**

Radiotherapy is administered after full recovery from surgical resection, usually after 5 weeks of BCS. Patients will receive computed tomography-based 3-dimensional treatment planning. The total dose to the breast is 40.05 Gy in 15 fractions. The use of intensity-modulated radiotherapy and deep inspiration breath hold techniques is permitted. No tumor bed boost or regional nodal irradiation shall be delivered.

Target contouring of the CTV-breast is performed according to the ESTRO-guidelines. An additional margin for inter- and intrafractional positioning uncertainties of 5-10 mm is added to

generate the PTV-breast. The PTV-breast\_EVAL (generated by subtraction of the 3 mm below the skin from the PTV-breast) should receive 95%-107% of the prescribed dose.

| Organ at risk        | Dose constraints                                                                                         |
|----------------------|----------------------------------------------------------------------------------------------------------|
| Heart                | $D_{\text{mean}} < 3 \text{ Gy}$ , $D_{\text{max}} < 30 \text{ Gy}$ (minor violation $< 40 \text{ Gy}$ ) |
| Ipsilateral Lung     | $D_{\text{mean}} < 8 \text{ Gy}$ , $V_{20\text{Gy}} < 10\%$ (minor violation $< 15\%$ )                  |
| Contralateral Breast | $D_{\text{mean}} < 3 \text{ Gy}$ , $D_{\text{max}} < 20 \text{ Gy}$                                      |
| Spinal cord          | $D_{\text{max}} < 45 \text{ Gy}$                                                                         |

Dose constraints of normal tissue will be respected according to QUANTEC reports (Bentzen et al. 2010; Marks et al. 2010).

### 6.3 Randomization

After initiation of the study, patients will consecutively be screened and eligible patients will be enrolled into the study. To achieve comparable intervention groups, patients will be allocated in a concealed fashion in a 1:1 ratio by means of randomisation using a centralised web-based tool ([www.randomizer.at](http://www.randomizer.at)). Randomization will be stratified with respect to invasive tumor size ( $\leq 1 \text{ cm}^3$ ,  $> 1 \text{ cm}^3$ ) and age ( $\leq 60$  years,  $> 60$  years). Block randomisation with varying block lengths will be performed to achieve in total equal group sizes.

### 6.4 Study visits

After screening of patients for inclusion and exclusion criteria and having received informed consent, appropriate patients will be recruited to the trial. Study relevant data will be collected and patient history will be assessed. Patients will be randomized 1:1 to one of the two study arms. The baseline visit (To) will be scheduled -7 to -1 day before planned treatment start. During the baseline visit (To) a clinical assessment as well as analysis of cosmesis and quality of life including fatigue is planned (and FACIT Fatigue Assessment Questionnaires, see 6.4). Patients will also receive photographic documentation for cosmetic assessment.

Patients in arm A are treated with BCS followed by hypofractionated WBI with a total dose of 40.05 Gy in 2.67 Gy single doses 5 weeks (+/- 2 week) after surgery when wound healing is completed. Patients treated in arm B will receive BCS followed by intermediate single-shot IOERT to the tumor cavity with a dose of 21 Gy prescribed to the 90%-isodose line.

Both groups will be evaluated after BCS at 5 weeks after treatment start (Study Visit 1), to assess to potential influence of IORT on fatigue (secondary endpoint). In group A this time point corresponds to 5 weeks after BCS, just before the start of RT; in group B this corresponds to 5 weeks after BCS incl. IORT.

After the first study visit patients will receive regular follow-up visits based on the standard follow-up program of current German guidelines. The second, third, fourth and fifth study visits are planned 12 weeks (primary endpoint), 6 months, 2 and 5 years (secondary endpoints) after the treatment start. These visits will include a clinical assessment as well as analysis of quality of life including fatigue (EORTC and Fatigue Assessment Questionnaires, BREAST-Q and BCTOS, see below for details). Photographic assessment of cosmetic results is also planned except for the last visit after 5 years. The last subject in (LSI) will be followed 5 years after baseline. This is considered the final study visit.

Treatment within this trial includes in both arms therapy approaches that are standard-of-care, and hence the patients require no additional time for treatment. The follow-up visits are implemented in the clinical routine, with the exception of baseline visit 0 in group A. The clinical and quality of life assessments including detailed analysis of fatigue as well as the photographic documentation of cosmesis as part of follow-up require an additional 30 minutes approximately per visit.

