### Objectives

#### Primary Endpoint:

Between group-change in fatigue from baseline (before treatment start/surgery) compared to 12 weeks after treatment start as assessed by the FACIT Fatigue Scale questionnaire.

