#### - Baseline Visit (To)

Baseline Visit will be performed after inclusion of the patient into the study protocol. The baseline visit will be scheduled -7 to -1 day before planned treatment start/BCS.

The following examinations will be performed:

- Clinical assessment using CRF
- Quality of life using the EORTC QLQ-C30, BREAST-Q and BCTOS
- Fatigue assessment using the Fatigue Assessment Questionnaire (FACIT – Fatigue Scale)
- Photographic documentation for cosmetic assessment

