#### **14.4 Patient insurance**

Since only clinically established therapies and diagnostics are used within the study, there is no study-specific insurance. As for treatments outside of studies, this means that study participants are not insured for the health damage or other adverse effects that they might experience in connection with participation in this study at the University Hospital Heidelberg, unless the physician or his staff meets culpable misconduct. Intent and negligence are to be regarded as culpable misconduct.

The study participants are not accident insured on the way to and from, as well as during an outpatient irradiation, with the exception of study-related appointments (i.e. TO in group A (baseline visit)).

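### The protocol does not require the baseline FACIT score before randomisation, so a self-reported value used in the confirmatory model may be influenced by knowledge of the allocated arm

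*Protocol*

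**What the plan says.** **Order of steps.** Section 6.4 runs from screening and consent to recruitment and then: "Patients will be randomized 1:1 to one of the two study arms. The baseline visit (To) will be scheduled -7 to -1 day", counted back from the start of treatment. The FACIT is assigned to that visit: "During the baseline visit (To) a clinical assessment as well as analysis of cosmesis and quality of life including fatigue is planned". The T0 entry in the same section says "Baseline Visit will be performed after inclusion of the patient into the study protocol", and the work-flow table also places T0 after enrolment.

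**T0 differs by arm.** Section 6.4 says of the visit schedule: "The follow-up visits are implemented in the clinical routine, with the exception of baseline visit 0 in group A". Section 14.4 makes an exception to the lack of accident cover: "with the exception of study-related appointments (i.e. TO in group A (baseline visit".

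**What baseline must precede.** The synopsis defines the primary endpoint as "Between group-change in fatigue from baseline (before treatment start/surgery) compared to 12 weeks after treatment start". It ties baseline to surgery, not to randomisation.

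**Masking.** Section 6.3 says "patients will be allocated in a concealed fashion in a 1:1 ratio by means of randomisation using a centralised web-based tool". That conceals the upcoming assignment. No blinding after assignment is described, and one intraoperative dose cannot be mistaken for 15 later fractions.

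**Use of the score.** Under section 10.2.2 the dependent variable is change in fatigue score from baseline to week 12. The model terms are treatment group, baseline score, tumour size and age. Section 7.1.1 describes the FACIT as a 13-item self-assessment over the past 7 days, scored 0 to 52 with higher scores better.

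**The concern.** Covariate adjustment in a randomised trial is safe because assignment cannot affect the covariate. A self-reported score taken after an unmasked allocation loses that protection. A woman who has just learned that she will have one dose during surgery, or several weeks of outpatient treatment, may rate her past week differently. With a 7-day recall period and a visit 7 to 1 days before surgery, part or all of the period rated could fall after she learned her arm.

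The confirmatory estimate is at stake. A baseline difference caused by allocation is not chance imbalance, and adjusting for it carries part of it into the treatment effect. A later statistical analysis plan cannot recover a pre-allocation score that was never collected.

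**Working it through.** **Step 1: the plan's own figure.** Section 10.1 gives a difference of 6 points, SD 12, two-sided alpha 0.05, power 0.90, 86 per group (172) and 15% dropout (202).
- Exact two-sample t-test power is 89.99% at 85 per group and 90.3% at 86, so 86 per group (172) is reproduced.
- Dropout: 172 / 0.85 = 202.4, stated as 202.

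The sample size is not in dispute.

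**Step 2: the bias.** Let Y0 and Y2 be the T0 and week-12 scores and b the slope of Y2 on Y0. Modelling Y2 - Y0 with Y0 as a covariate gives the same treatment coefficient as modelling Y2 with Y0 as a covariate; only the coefficient of Y0 changes, from b to b - 1. Suppose knowing the arm shifts recorded T0 by d (APBI minus WBI) without altering Y2. Then

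expected adjusted effect = true effect - b x d.

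Higher scores mean less fatigue. If women allocated to WBI report worse fatigue at T0, d is positive and the bias works against APBI. If they report better, it favours APBI. The documents do not say which.

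**Step 3: assumed inputs.** The protocol gives neither d nor b. I take d = 1 to 3 points, b = 0.3 to 0.7, and SD 12 at both times, so that b equals the correlation. Then

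SE = 12 x sqrt(1 - b²) x sqrt(2/86).

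**Step 4: worked case, d = 2 and b = 0.5.**
- Bias = 0.5 x 2 = 1.0 point, or 1/6 = 17% of the target.
- SE = 12 x sqrt(0.75) x sqrt(2/86) = 10.39 x 0.1525 = 1.585.
- Type I error: 1.0 / 1.585 = 0.631; Phi(0.631 - 1.96) + Phi(-0.631 - 1.96) = 0.092 + 0.005 = 0.097.
- Power without a shift: Phi(6/1.585 - 1.96) = 0.966.
- Power if the bias opposes a true 6: Phi(5/1.585 - 1.96) = 0.884.

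**Step 5: range (normal approximation, 86 per arm).**

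| b | d | Bias (points) | % of 6 | Two-sided type I error | Power, no shift | Power, opposing shift |
|---|---|---|---|---|---|---|
| 0.3 | 1 | 0.3 | 5 | 0.053 | 0.930 | 0.904 |
| 0.3 | 2 | 0.6 | 10 | 0.064 | 0.930 | 0.871 |
| 0.3 | 3 | 0.9 | 15 | 0.081 | 0.930 | 0.832 |
| 0.5 | 1 | 0.5 | 8 | 0.061 | 0.966 | 0.935 |
| 0.5 | 2 | 1.0 | 17 | 0.097 | 0.966 | 0.884 |
| 0.5 | 3 | 1.5 | 25 | 0.157 | 0.966 | 0.810 |
| 0.7 | 1 | 0.7 | 12 | 0.083 | 0.996 | 0.982 |
| 0.7 | 2 | 1.4 | 23 | 0.188 | 0.996 | 0.941 |
| 0.7 | 3 | 2.1 | 35 | 0.362 | 0.996 | 0.847 |

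**Step 6: simulation check (5,000 trials per setting).** At b = 0.5 and d = 2 the mean estimate under no effect was -0.99, with type I error 0.093 and power 0.874. Without a shift, type I error was 0.047 (b = 0.5) and 0.055 (b = 0.7).

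**The case against.** **The sequence is inferred.** No sentence says outright that T0 follows randomisation or that the patient knows her arm when she completes the FACIT. Section 6.4 is a narrative, and it mentions collecting study data before the randomisation sentence. The term open-label does not appear in the text at hand. This stands as a limit on certainty. It does not dispose of the point: a visit described as outside routine "with the exception of baseline visit 0 in group A" makes sense only if the arm is known when the visit is arranged, and no text requires the opposite order.

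**The shift is hypothetical.** Nothing in the documents anchors d, and its direction is open. This also stands, so the figures above are illustrations.

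**Week 12 is exposed too.** The T2 self-report is equally unmasked, and moving T0 does not change that. True, but this is no reason to leave the baseline exposed as well.

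A reader might infer more than the documents support:
- *Power falls from 90% to 78%.* That pairs a bias from the adjusted model with the power of an unadjusted t-test. With b = 0.5 the residual SD is 10.4, and the consistent figures are about 97% and 88%.
- *Using baseline both in the change score and as a covariate doubles the harm.* It does not; step 2 shows a single bias term.
- *T0 is no longer a pre-treatment value.* It still precedes surgery. The problem is that it may follow randomisation.
- *Group A is questioned in a different setting.* The text says only that its T0 lies outside routine.
- *All secondary change scores are biased.* Section 10.2.3 treats secondary outcomes descriptively, and no change-from-baseline secondary endpoints are defined.
- *Women without a T0 score are left unhandled.* A missing baseline makes the change score missing, which the multiple imputation in section 10.2.2 covers. Further detail belongs to the statistical analysis plan.

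**Conclusion.** The point holds as a gap in the design text: the protocol describes randomisation before T0, implies that the arm is known when T0 is arranged, and never requires the baseline FACIT before allocation or its disclosure. The primary estimate is therefore open to a bias of -b x d, of unknown sign. Over the assumed ranges this is 0.3 to 2.1 points, or 5% to 35% of the 6-point target; the central illustration is 1.0 point. The size rests on assumed d and b, SD 12 at both times, and a shift confined to the T0 report. The documents do not show that such a shift will occur, so this is an avoidable risk and not a demonstrated bias. It merits correction because the confirmatory analysis depends on this score and the remedy is cheap.

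**What to change.** In section 6.4 (the narrative and the T0 entry) and in the work-flow table, require the FACIT, EORTC QLQ-C30, BREAST-Q, BCTOS and photographs after consent and before randomisation, by the same procedure in both arms. At minimum, require them before the allocation is disclosed to the patient. Adjust the -7 to -1 day window as far as this needs, and reconcile the group-A-only wording in sections 6.4 and 14.4. If practice is already baseline-first, the text should say so.

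The cost is a somewhat longer gap between baseline and surgery, and a few baseline assessments from women who are then not randomised. The 172 evaluable and 202 randomised patients are unchanged. Whether the change would spare group A an extra visit cannot be told from the documents; T0 might instead become non-routine in both arms.

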#### - Screening –

Screening for the study will be performed prior to inclusion of the patient into the study. All inclusion and exclusion criteria must be fulfilled.

#### - Baseline Visit (To)

Baseline Visit will be performed after inclusion of the patient into the study protocol. The baseline visit will be scheduled -7 to -1 day before planned treatment start/BCS.

The following examinations will be performed:

- Clinical assessment using CRF
- Quality of life using the EORTC QLQ-C30, BREAST-Q and BCTOS
- Fatigue assessment using the Fatigue Assessment Questionnaire (FACIT – Fatigue Scale)
- Photographic documentation for cosmetic assessment

#### - Study Visit (T1)

The first study visit is scheduled 5 weeks (+/- 2 week) after treatment start in both groups. As group B receives irradiation with intraoperative electron radiotherapy, this visit will also take place 5 weeks after RT for group B.

The following examinations will be performed:

- Clinical assessment using CRF
- Quality of life using the EORTC QLQ-C30, BREAST-Q and BCTOS
- Fatigue assessment using the Fatigue Assessment Questionnaire (FACIT – Fatigue Scale)

- Photographic documentation for cosmetic assessment
- Assessment of adverse events

#### -Study Visit (T2), primary endpoint

The second study visit is planned 12 weeks (+/- 2 week) after treatment start for both groups. For group A, this is 7 weeks after hypofractionated WBI, while for group B this visit is 12 weeks after IORT.

The following examinations will be performed:

- Clinical assessment using CRF
- Quality of life using the EORTC QLQ-C30, BREAST-Q and BCTOS
- Fatigue assessment using the Fatigue Assessment Questionnaire (FACIT Fatigue Scale)
- Photographic documentation for cosmetic assessment
- Assessment of adverse events

#### -Study Visit (T3)

The third study visit is scheduled 6 months (+/- 2 weeks) after treatment start. The following examinations will be performed:

- Clinical assessment using CRF
- Quality of life using the EORTC QLQ-C30
- Fatigue assessment using the Fatigue Assessment Questionnaire (FACIT Fatigue Scale)

#### -Study Visit (T4)

The fourth study visit is scheduled 2 years (+/- 2 months) after BCS. The following examinations will be performed:

- Clinical assessment using CRF
- Quality of life using the EORTC QLQ-C30, BREAST-Q and BCTOS
- Fatigue assessment using the Fatigue Assessment Questionnaire (FACIT Fatigue Scale)
- Photographic documentation for cosmetic assessment

#### -Study Visit (T5)

The fifth study visit is scheduled 5 years (+/- 3 months) after BCS. The following examinations will be performed:

- Clinical assessment using CRF
- Quality of life using the EORTC QLQ-C30
- Fatigue assessment using the Fatigue Assessment Questionnaire (FACIT Fatigue Scale)

| Work-Flow                                         | Baseline                       | Follow-up        |                          |                          |                         |                         |
|----------------------------------------------------------|---------------------------------------|-------------------------|--------------------------|--------------------------|-------------------------|-------------------------|
|                                                          | To                             | T1               | T2                | T3                | T4               | T5               |
|                                                          | Baseline visit after enrolment | 5 weeks after TS | 12 weeks after TS | 6 months after TS | 2 years after TS | 5 years after TS |
| Medical history                                   | X                                     | X                       | X                        | X                        | X                       | X                       |
| Fatigue Assessment (FACIT Fatigue Scale)          | X                                     | X                       | X                        | X                        | X                       | X                       |
| EORTC QLQ-C30                                     | X                                     | X                       | X                        | X                        | X                       | X                       |
| BREAST-Q and BCTOS                                | X                                     | X                       | X                        |                          | X                       |                         |
| Documentation of medication                       | X                                     | X                       | X                        | X                        | X                       | X                       |
| Documentation of AEs                              |                                       | X                       | X                        |                          |                         |                         |
| Photographic documentation of cosmetic assessment | X                                     | X                       | X                        |                          | X                       |                         |
| CRF Form                                          | X                                     | X                       | X                        | X                        | X                       | X                       |

## 7. Trial Methods

The primary objective is to compare change on the overall fatigue scale from baseline (before surgery) to week 12 after treatment start between breast cancer patients treated with hypofractionated WBI or intraoperative APBI. Secondary analysis include local tumor control, regional and distant recurrence rates, disease-free as well as overall survival, assessment of acute and chronic toxicity, quality of life and cosmesis. Furthermore, gene expression analysis using the Prosigna/PAM50-assay will be performed as a secondary endpoint to evaluate the potential prognostic/predictive impact on choice of radiotherapy modality.

### 7.1 Assessment of Efficacy Parameters

#### 7.1.1 Primary endpoint: Fatigue Testing

The primary endpoint is change of fatigue after APBI or WBI from baseline to 12 weeks after treatment start (T2 vs. T0). Fatigue will be assessed with the help of the Functional Assessment of Chronic Illness Therapy (FACIT) Fatigue Scale, which consists of a 13-item multidimensional self-assessment form evaluating quantity of fatigue and distress. The FACIT Fatigue Scale is extensively applied in cancer patients. Using the FACIT Fatigue Scale questionnaire, patients are asked to indicate how frequent each item was for them “during the past 7 days” applying a 5-point scale (“not at all” to “very much”). The range of possible scores is 0–52, with 0 being the worst possible score and 52 the best.

**Patient Administration time:** 5-10 min

